## Project Implementation Timeline

| # | Phase                                        | Duration | Monthly Progress Tracking (1-10) |
|---|----------------------------------------------|----------|----------------------------------|
| 1 | Proposal Writing                             | 1 month  | 10 9 8 7 6 5 4 3 2 1      |
| 2 | Proposal Approval & Ethical Code Acquisition | 1 month  | 10 9 8 7 6 5 4 3 2 1      |

| # | Phase                                   | Duration | Monthly Progress Tracking (1-10) |
|---|-----------------------------------------|----------|----------------------------------|
| 3 | Implementation & Data Collection        | 6 months | 10 9 8 7 6 5 4 3 2 1      |
| 4 | Data Analysis                           | 1 month  | 10 9 8 7 6 5 4 3 2 1      |
| 5 | Results Reporting & Article Publication | 1 month  | 10 9 8 7 6 5 4 3 2 1      |

### 3. Interventions

#### All Participants Receive:

- **Standard Urotherapy (10 sessions, 20 mins/session, 2x/week):**
  - Education on urinary tract function
  - Fluid management (1.5–2 L/day)
  - Scheduled voiding (every 2–3 hours)
  - Proper toileting posture (spinal alignment, foot support)
  - Pelvic floor muscle training (10-sec contraction + 30-sec relaxation).

#### Group-Specific Protocols:

| Component           | Active IFC Group                                      | Sham IFC Group                      |
|---------------------|-------------------------------------------------------|-------------------------------------|
| Device              | Novin 2-channel (Iran)                                | Identical device                    |
| Parameters          | 4,000 Hz carrier, 80–160 Hz beat                      | Same setup                          |
| Electrode Placement | Cross-shaped (pubic symphysis + ischial tuberosities) | Identical placement                 |
| Intensity           | Strong but comfortable                                | Initial sensation (1 min), then OFF |

| Component        | Active IFC Group                 | Sham IFC Group           |
|------------------|----------------------------------|--------------------------|
| Session Duration | 30 mins IFC + 20 mins urotherapy | 1 min IFC + 29 mins sham |

## 4. Outcome Measures

### Primary Endpoints:

1. **Uroflowmetry:** Qmax, voiding time, PVR (ultrasound).
2. **ICIQ-FLUTS:** Symptom severity.

### Secondary Endpoints:

- PFDI-20 (pelvic floor distress).
- PGIC (patient-reported improvement).
- 3-day voiding diary (24-hour frequency).

### Assessment Timeline:

- **Baseline:** Pre-treatment.
- **Post-Treatment:** After 10 sessions (5 weeks).
- **Follow-Up:** 3 months post-treatment.

## 6. Ethical Considerations

- **Informed Consent:** Obtained prior to randomization.
- **Sham Control:** Ethical approval for minimal IFC exposure (1 min).
- **Post-Trial Access:** Active treatment offered to sham group if significant benefits observed.

## Key Methodological Strengths

1. **Robust Blinding:** Sham protocol minimizes placebo effects.
2. **Standardized Protocols:** Identical urotherapy for both groups ensures comparability.
3. **Objective + Subjective Measures:** Combines urodynamics (Qmax, PVR) with validated questionnaires (ICIQ-FLUTS).
4. **Longitudinal Design:** 3-month follow-up assesses sustainability.

### Limitations:

This study may encounter patient attrition due to the follow-up period. In order to reduce this issue, an effort has been made to keep the follow-up period as short as possible and to clearly explain to patients the importance of returning to a urologist after the follow-up period.

### **Protocol Deviations Management**

- **Non-Adherence:** Participants missing >2 sessions excluded from per-protocol analysis.
- **Adverse Events:** Documented and reported to ethics board (e.g., skin irritation from electrodes).

This protocol aligns with CONSORT guidelines for non-pharmacological trials. Let me know if you need additional operational details!

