### **Randomization and Blinding**

- **Randomization:** Patients will be allocated with 1:1 ration into treatment (real IFC) or control (sham IFC) groups using computer-generated block randomization (block size = 4).
- **Blinding:**
  - **Patients:** Sham IFC will be applied for 1 minute (at perceptible but non-therapeutic intensity) to mimic active treatment. Real IFC will be applied with the strong tolerable intensity.
  - **Outcome assessor (urologist):** Blinded to group assignment.
  - **Therapist:** Unblinded due to treatment nature.
- **Allocation concealment:** Sealed opaque envelopes (prepared by an independent person) will ensure concealment until intervention begins.

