### **Statistical Analysis**

Descriptive information regarding the demographic characteristics of individuals in both groups will be given as means (standard deviations) for quantitative variables and as frequencies (percentages) for qualitative variables. For comparing of each demographic variable between the two study groups, the independent t-test for normally distributed quantitative variables and the Mann-Whitney test for non-normally distributed quantitative variables will be applied. The chi-square test will be conducted to compare qualitative variables.

The normality of the data in the study groups will be tested using the Shapiro-Wilk test. To comprehensively examine the extracted data, the following procedures will be carried out, as elaborated below.

To compare the mean of each variable in both groups before the intervention, two weeks after the intervention, and after a three-month follow-up period, the two-way repeated measures ANOVA will be employed, assuming the data are normally distributed. In the case of non-normality, a nonparametric equivalent will be used.

For the comparison of the mean of the variables between both groups at every time point (before the intervention, at two weeks after the intervention, and after a three-month follow-up), the two independent sample t-test will be used if the data is normally distributed and the Mann-Whitney test if the data is distributed non-normally.

To determine differences in the mean of the variables of both groups over the study period, the one-way repeated measures ANOVA will be used. In the presence of a statistically significant difference in the variable mean over time, the post hoc test with Bonferroni and Tukey corrections will be utilized. The data will be analyzed using SPSS version 26 software. The significance level in this study is assumed to be 5%.

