### 1. PVR:

- $H_0$ : There is no significant difference in mean PVR before and after treatment in the real IFC group.
- $H_0$ : There is no significant difference in mean PVR after treatment between the real IFC and sham IFC groups.

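### The only analysis population the protocol names excludes women by attendance after randomisation, and it does not say whether that set is primary or supportive

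*Protocol*

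**What the plan says.** Under Protocol Deviations Management the protocol states: "Participants missing >2 sessions excluded from per-protocol analysis". No other analysis population appears in the document: there is no intention-to-treat or full analysis set, and no statement that women are analysed in the arm to which they were allocated.

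The Statistical Analysis section lists the tests without a population. For the three time points, for example, "the two-way repeated measures ANOVA will be employed, assuming the data are normally distributed". The between-arm hypotheses name none either; the one for residual volume reads "There is no significant difference in mean PVR after treatment between the real IFC and sham IFC groups".

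Allocation is randomised: "Patients will be allocated with 1:1 ration into treatment (real IFC) or control (sham IFC) groups using computer-generated block randomization". The sessions that count towards the exclusion come afterwards, on a schedule of "10 sessions, 20 mins/session, 2x/week". The arms differ in what is felt. In the active arm, "Real IFC will be applied with the strong tolerable intensity"; the sham arm's entry in the Group-Specific Protocols table is "Initial sensation (1 min), then OFF". The therapist knows the allocation; the urologist who assesses outcome does not.

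**The concern.** Attendance is observed after randomisation and may be influenced by the treatment received. The active arm feels a strong current throughout, the sham arm feels one minute of it, and the therapist who sees the women at each session is unblinded. The reasons for missing sessions may therefore differ between arms and be related to how a woman is doing. If women are removed on that basis, those who remain in the two arms need not be comparable, even though the arms were comparable when allocated.

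The only inclusion rule a reader of this protocol can apply is the one that gives up the protection of randomisation. With 14 women per group, a few exclusions could move the estimated effect on residual volume, Qmax or symptom score, in either direction. Leaving the role of the set open also means it could be settled after results are known.

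**Working it through.** **Inputs from the protocol.** 14 per group at 80% power and 95% confidence (Sample Size Calculation Method); 5% significance level (Statistical Analysis); 10 sessions, with exclusion for missing more than 2, so the per-protocol set needs 8 or more attended.

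**Inputs assumed, because the protocol gives none.** The proportion excluded in each arm; the correlation ρ between a latent attendance score and the outcome (0.3 to 0.7); two-sided testing; no true treatment effect.

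**1. The plan's own figure.** The 14 per group cannot be reproduced, because the endpoint, effect and SD behind it are not stated. For a comparison of two means it implies a standardised difference of

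d = √(2/14) × (1.960 + 0.842) = 0.378 × 2.802 = 1.06.

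**2. Bias from selection on attendance.** Let the outcome have mean 0 and SD 1 in both arms, with higher values better. If the fraction q with the lowest attendance is excluded, the expected mean of those retained is

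ρ × φ(z_q) / (1 − q),

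where φ is the standard normal density and z_q the q-th normal quantile.

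- q = 0.30: 0.3477 / 0.70 = 0.497
- q = 0.10: 0.1755 / 0.90 = 0.195
- Difference: 0.302 × ρ

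This gives 0.09, 0.15 and 0.21 SD at ρ = 0.3, 0.5 and 0.7. Reversing the arms reverses the sign. Equal q with the same ρ in both arms gives 0.

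A simulation with 14 per arm, 40,000 replicates per case and a two-sample t-test on the women retained agrees:

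| Excluded, real vs sham | Bias, real minus sham (SD), ρ = 0.3 to 0.7 | Two-sided error |
|---|---|---|
| none | about 0 | about 5% |
| 15% vs 15% | about 0 | about 5% |
| 20% vs 10% | +0.05 to +0.10 | 4.8% to 5.7% |
| 30% vs 10% | +0.09 to +0.21 | 5.4% to 8.3% |
| 10% vs 20% | -0.04 to -0.11 | 5.2% to 5.9% |
| 10% vs 30% | -0.09 to -0.22 | 5.4% to 8.1% |

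With 30% vs 10% excluded, a false result in favour of IFC occurs in 3.8% to 7.6% of trials, against a nominal 2.5%. With 10% vs 30%, a false result against IFC occurs in 3.9% to 7.5%. At ρ = 0 the bias is about 0 whatever the exclusion rates.

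**3. Power lost through exclusions.** By the normal approximation, power = Φ(d × √(n/2) − 1.960) with d = 1.059:

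- n = 14: Φ(2.802 − 1.960) = Φ(0.842) = 80%
- n = 12: Φ(2.594 − 1.960) = Φ(0.634) = 74%
- n = 10: Φ(2.368 − 1.960) = Φ(0.408) = 66%

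**The case against.** The strongest reply is that the quoted sentence is an ordinary definition of a per-protocol set and is not wrong in itself. It does not call that analysis primary or sole, and does not remove these women from the tests in the Statistical Analysis section, which refers simply to both groups. A SAP that is not at hand may name a full set, and the protocol claims alignment with CONSORT. All of this stands. A reader might infer that the trial will be judged on the per-protocol set alone; the text does not say so. What remains is that the protocol did fix one population rule, that this rule selects on behaviour after randomisation, and that its role is left open.

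A reader might also infer that the rule favours IFC, for instance because women who tolerate the current badly leave the active arm. The document does not support a direction. Sham women who feel no benefit may equally stop coming, which would bias against IFC. Active intensity is set to each woman's tolerance, and the Group-Specific Protocols table describes it as comfortable. Skin irritation, the adverse event given as an example, cannot be tied to the active arm, since device and electrode placement are identical in both.

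The Limitations section does not help the case either. "This study may encounter patient attrition due to the follow-up period" concerns losses over the follow-up period, which is a missing-outcome question and says nothing about missed treatment sessions.

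Finally, the sizes rest on assumed rates and correlations, and several cases leave the error rate close to 5%. That is fair: they show what could happen, not what is expected.

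**Conclusion.** The point holds as a gap in what the protocol fixes. Its only named analysis population excludes women on attendance after randomisation, its tests have no stated population, and the status of the per-protocol set is undefined. If the rule were applied to the real-versus-sham comparisons, they would no longer be randomised comparisons.

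The possible bias is modest and of unknown sign. It is close to zero when both arms lose the same share of women for the same kind of reason, and about 0.1 to 0.2 SD in either direction when one arm loses 30% and the other 10%. Equal counts alone do not guarantee zero, because the women leaving each arm may be of different kinds. Two or four exclusions per arm would also take power from 80% to about 74% or 66% at the difference the sample size implies.

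These figures assume no true effect (for the bias), normal outcomes, a correlation of 0.3 to 0.7 and exclusion rates that the protocol does not give. They do not show that the trial will favour IFC, or that the sponsor intends a per-protocol primary analysis. The matter should be corrected, and the correction costs little.

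**What to change.** In Statistical Analysis and in Protocol Deviations Management, state that the primary real-versus-sham comparisons include all randomised women with outcome data, in their assigned arm, whatever number of sessions they attended. Keep the per-protocol set, with its existing threshold, as a supportive analysis only, and report by arm how many women it excludes. Any SAP should carry the same wording, and the change should be made before results by arm are seen.

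This takes one or two sentences and needs no extra patients or visits. The small downside is a somewhat diluted estimate of the effect of a full course if several women miss sessions; the supportive analysis addresses that question. Women with no outcome data remain a separate missing-data matter that this change does not resolve.

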### **Specifications of Data Collection Tools and Collection Methods**

#### **1) Researcher-Developed Questionnaire for Collecting Demographic Information**

A questionnaire designed by the researchers of this study to collect patients' demographic characteristics including age, height, weight, and body mass index (BMI).

#### **2) Uroflowmetry Test**

Urodynamic studies are considered the gold standard for diagnosing urinary voiding disorders. This test provides a functional assessment of the lower urinary tract, beginning with simple non-catheter uroflowmetry followed by measurement of post-void residual urine volume using full and empty bladder ultrasound (10).

Uroflowmetry is a non-invasive test that evaluates urinary voiding function before treatment and during follow-ups. In this test, the patient urinates into a special device that measures urine flow rate. At the end of the test, a urine flow curve is plotted and quantitative parameters are reported (11, 31).

#### **3) 3-Day Voiding Diary (32)**

A form where the patient records the number of urinations, volume of urine voided each time, incontinence episodes, pad usage (in cases of incontinence), catheter use (in cases of urinary retention), as well as the amount and type of fluids consumed over three days. For retention disorders, using a 3-day or longer voiding diary is recommended (9, 33).

#### **4) PFDI-20 Questionnaire (34)**

This questionnaire, recommended by the International Continence Society, contains 20 questions across three different domains assessing the severity of pelvic floor disorders. The total score is 300, with each domain scored out of 100, where higher scores indicate more severe symptoms.

#### **5) Persian Version of ICIQ-FLUTS Questionnaire (35)**

A validated questionnaire for assessing lower urinary tract symptoms and their impact on quality of life, containing 12 questions across three domains: filling phase symptoms, voiding phase symptoms, and incontinence symptoms.

#### **6) GRCS Questionnaire**

A questionnaire for evaluating patient changes after treatment, where patients rate their changes on a 7-point scale from "much worse" to "much better" (33).

#### **Sample Size Calculation Method**

Based on the study by Kajbafzadeh et al. and considering a 95% confidence level and 80% test power, the sample size was calculated as 14 participants per group (20).

#### **Study Limitations and Mitigation Strategies**

The main limitation of the study is potential sample attrition due to the follow-up period. To minimize this issue, a short follow-up duration was selected, and the importance of follow-up visits was thoroughly explained to patients.

Does the research involve specialized tests or specific techniques?

Yes

Knowledge Translation

Target Audience:

- Healthcare providers (physicians, nurses, midwives, etc.)

If the target audience is policymakers/administrators:

[No explanation provided]

If the target audience is healthcare providers:

If interventional current therapy proves effective in significantly improving clinical symptoms and urodynamic findings in women with voiding dysfunction, pelvic floor disorder specialists (physiotherapists, urologists, pelvic medicine fellows,

gynecologists) could incorporate this treatment into their practice for patients with urinary disorders.

If the target audience is the general public/patients:

[No explanation provided]

If the target audience is companies/industries:

[No explanation provided]

If the target audience is other organizations:

[No explanation provided]

Knowledge Dissemination Methods:

- Presentation at international conferences/seminars
- Presentation at domestic conferences/seminars
- Sending summary/full report or resulting articles to potential users
- Publication in international scientific-research journals
- Publication in domestic scientific-research journals
- Posting full report/summary on website for potential users

Explanation of Implementation Methods:

All therapeutic groups in pelvic floor disorders including physiotherapists, urologists, and gynecologists can benefit from the study results for treating voiding dysfunction. Physiotherapists can use the mentioned methods upon physician referral and add effective treatment protocols. The principal investigator, as a pelvic floor specialist physiotherapist, can utilize superficial electrical stimulation in specified areas to improve voiding dysfunction after publishing results and confirming treatment efficacy.

Primary Stakeholder (Individual/Organization):

Patients with voiding dysfunction

- Importance score (1-5): 5
- Power score (1-5): 2

Secondary Stakeholder:

Physiotherapy department, Rehabilitation Faculty, Iran University of Medical Sciences

- Importance score: 3
- Power score: 2

Tertiary Stakeholder:

Pelvic floor disorder therapists and physiotherapists

- Importance score: 5
- Power score: 1

Quaternary Stakeholder:

Urologists, gynecologists, and pelvic medicine fellows

- Importance score: 4
- Power score: 3

Design variables

| Variable Name                   | Variable Role | Variable Type           | Scientific Definition                                                                                                                                                | Measurement Method | Scale |
|---------------------------------|---------------|-------------------------|----------------------------------------------------------------------------------------------------------------------------------------------------------------------|--------------------|-------|
| Post-void residual volume (PVR) | Dependent     | Quantitative/Continuous | Refers to urine remaining in the bladder after voiding. Determined using catheterization after complete voiding (5,11). PVR >100 mL suggests urinary retention (20). | Ultrasound         | mL    |

| Variable Name                        | Variable Role | Variable Type           | Scientific Definition                                                                                                                                                                                                                         | Measurement Method  | Scale  |
|--------------------------------------|---------------|-------------------------|-----------------------------------------------------------------------------------------------------------------------------------------------------------------------------------------------------------------------------------------------|---------------------|--------|
| Maximum urinary flow rate (Qmax)     | Dependent     | Quantitative/Continuous | The peak urinary flow rate, denoted as Qmax in studies, represents the highest measured urine flow velocity reported in mL/sec (10). Reduced Qmax indicates voiding dysfunction. Values <15 mL/sec in women suggest voiding dysfunction (13). | Uroflowmetry        | mL/sec |
| Toilet use frequency                 | Dependent     | Quantitative/Discrete   | -                                                                                                                                                                                                                                             | 3-day voiding diary | -      |
| Lower urinary tract symptom severity | Dependent     | Quantitative/Continuous | Subjective symptoms perceived by patients/caregivers that prompt treatment-seeking, typically obtained through history-taking (1).                                                                                                            | Persian ICIQ-FLUTS  | -      |
| Patient-reported treatment changes   | Dependent     | Quantitative/Discrete   | Global assessment of disease status using standardized indices that report overall symptom                                                                                                                                                    | Persian PGI-C       | -      |

| Variable Name                         | Variable Role | Variable Type           | Scientific Definition                                                                                  | Measurement Method    | Scale |
|---------------------------------------|---------------|-------------------------|--------------------------------------------------------------------------------------------------------|-----------------------|-------|
|                                       |               |                         | changes post-treatment (33).                                                                           |                       |       |
| Urinary incontinence symptom severity | Background    | Quantitative/Continuous | Subjective symptoms prompting treatment-seeking, typically qualitative data from patient history (27). | Persian ICIQ-FLUTS LF | -     |
| Age                                   | Background    | Quantitative/Discrete   | Chronological age calculated from birth date in years/months/days                                      | Questionnaire         | years |
| Weight                                | Background    | Quantitative/Continuous | The mass of a person's body                                                                            | Standard scale        | kg    |
| Height                                | Background    | Quantitative/Continuous | Vertical distance from foot to head in standing position                                               | Measuring tape        | cm    |

